The purpose of the present study is to evaluate the efficacy of the CO-oximetry technique, together with brief advice, in smoking cessation at month 12 in smokers in contemplative or pre-contemplative phase compared with brief advice alone. Furthermore, the study also aims to evaluate the efficacy of the CO-oximetry technique together with brief advice in the reduction of the number of cigarettes and in the variation of the motivation to quit smoking at month 12 in smokers in contemplative or pre-contemplative phase compared with brief advice alone.

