### Study population

The study population is made up of smokers ≥18 years that attend a primary care consultation for any medical problem.

Inclusion criteria will include smokers ≥18 years in the pre-contemplation or contemplation phases described by Prochaska and DiClemente. According to the WHO, a smoker is someone who has smoked daily at least during the past month, irrespective of the amount of cigarettes he/she has smoked. A smoker in the pre-contemplation phase is someone who is not aware that he/she has a problem or thinks he/she is not able to change, does not see his/her behaviour as a reason for concern, and does not consider changes within the next 6 months. A smoker in the contemplation phase is characterised by ambivalence, he/she simultaneously considers and rejects the idea of changing, oscillates between worry and lack of worry as well as between the motivations to change or to continue without changing, and intent to change is established in the long-term without specifying when [9]. Exclusion criteria will include smokers in the preparation phase (prepared to quit smoking in a month’s time); people with a terminal illness or whose health status does not allow them to understand the study or complete the informed consent either due to mental illness or transitory psychiatric deterioration at the moment of inclusion; pregnant or breastfeeding women.

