#### Secondary outcome measures

Point smoking cessation at month 6 and/or month 12 confirmed by a urine cotinine test; self-declared smoking cessation at months 6 and 12; reduction in the number of self-declared cigarettes consumed when smoking cessation is not accomplished at months 6 and 12; variation in the phase of process of smoking cessation: from pre-contemplation to contemplation or preparation phase, or from contemplation to preparation phase, at months 6 and 12.

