#### Independent measures

Type of intervention: brief advice or brief advice together with CO-oximetry. At baseline, the following information will be obtained: (a) socio-demographic variables: gender, age, social class measured by means of two indicators suggested by the Spanish Society of Epidemiology: educational level and occupation; (b) regarding the patient’s smoking behaviour: number of cigarettes/day and number of years the patient has been smoking (the number of packets/year will be calculated based on this information); concentration of nicotine and tar smoked currently (obtained from the type of tobacco consumed); number of times the patient has tried to quit smoking and reasons for relapse; maximum amount of time without smoking; tobacco consumption during work, with family and/or friends; physical dependency on nicotine using a simplified version of the Fagerström test; phase of the smoking cessation process: Prochaska and DiClemente phases (pre-contemplation, contemplation, preparation, cessation and relapse); any intervention to quit smoking during the past year; (c) other measures: consumption of other legal drugs (alcohol, psychopharmacological drugs); consumption of illegal drugs (cannabis, cocaine and others); basal disease associated with tobacco consumption (Chronic Obstructive Lung Disease, cancer, ischemic myocardiopathy, cerebrovascular disease); other cardiovascular risk factors (HTA, diabetes mellitus, dyslipidaemia, obesity); mental illness.

At months 6 and 12 the following data will be collected: Smoking behaviour/status (does the patient smoke or has he/she quit); date of smoking cessation, whether the patient has quit smoking; time interval without smoking between date of intervention till six month assessment; participation in a programme for smoking cessation since the beginning of the study.

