## Discussion

Smoking behaviour is one of the major public health problems. As such, all interventions that can be done to protect health and motivate smoking cessation are welcomed, especially if they are simple, non-aggressive, accessible and feasible [23]. If this intervention is performed in primary care, where 90% of the population come over 5 years, the population effect is highly relevant and of great benefit to Public Health.

Although our intervention is addressed to all current smokers, it has been specially designed for those smokers who, due to their great physical and psychological dependence and their balance between positive and negative smoking cessation factors, opt in favour of smoking maintenance. These smokers require forceful information directly related to the effects on their health to change the balance of these factors and allow an opportunity for smoking cessation to take place.

One of the limitations of studies evaluating personal risk relates to those cases in which the results generated by the technology used are normal and, in consequence, reinforce the smoker’s perception about the harmless effects of smoking. We think that the brief advice can minimize this.

The urine cotinine test could be perceived by patients as another intervention for smoking cessation and, therefore, have an effect on smoking cessation. We consider that carrying out the test on both groups minimises this effect.

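### The motivation outcome lists only forward phase moves, so it cannot register a contemplator who falls back to pre-contemplation

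*Protocol article*

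**What the plan says.** The second objective, at the end of the Background, is to evaluate the efficacy of CO-oximetry plus brief advice "in the variation of the motivation to quit smoking at month 12 in smokers in contemplative or pre-contemplative phase". It gives no direction.

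Under Secondary outcome measures the same idea becomes "variation in the phase of process of smoking cessation", followed by a list of the moves meant: "from pre-contemplation to contemplation or preparation phase, or from contemplation to preparation phase, at months 6 and 12". That is three moves, all towards quitting. Neither contemplation to pre-contemplation nor any move to cessation is listed, and no rule says how an unlisted move is scored.

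Four other places bear on this:

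- Study population: "Inclusion criteria will include smokers ≥18 years in the pre-contemplation or contemplation phases". Both phases are eligible, so a backward move is possible for part of the sample.
- Study population, on the contemplator: "oscillates between worry and lack of worry as well as between the motivations to change or to continue without changing".
- Discussion: a normal result may "reinforce the smoker’s perception about the harmless effects of smoking". The reply given is: "We think that the brief advice can minimize this".
- Independent measures: the phase recorded at baseline uses the "Prochaska and DiClemente phases (pre-contemplation, contemplation, preparation, cessation and relapse" scale. Under Study development, the dependent measures are collected again by telephone at 6 months, and the same questions are asked at 12 months.

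**The concern.** The outcome is narrower than the objective it serves. Variation can go either way, but a proportion built from the three listed moves can only record gains. The two-sided test in the Statistical analysis section does not repair this. It could show fewer forward moves in the intervention group, but not more backward moves, because those are never counted.

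The gap matters more here than in most cessation trials. The article itself names a route by which the tested technique could lower motivation, and that route exists only in the arm that receives a CO reading at inclusion. If high readings moved some smokers forward and normal readings moved others back, the outcome would report the first effect and omit the second.

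**Working it through.** **The plan's own figure.** No figure is given for the motivation outcome. The only stated size is 471 per group, for cessation at 5% versus 10%, two-sided alpha 0.05, power 0.80 and 10% loss. It reproduces with the arcsine formula: h = 2(arcsin √0.10 − arcsin √0.05) = 0.1925; n = 2(1.960 + 0.842)² / h² = 423.7; 423.7 / 0.90 = 470.8, so 471. It is used below only as the number per arm.

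**Who can move back.** Pre-contemplators are already at the lowest phase, so only baseline contemplators can regress. Their share, c, is not given and is ranged over 20%, 30%, 50% and 70%.

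**Assumed rates, for illustration only.** In the control group 20% of the arm move forward and 10% of contemplators move back. All 471 per arm are analysed. Net change is the forward proportion minus the backward proportion, with every move counted equally.

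**Formulas.** Forward-only difference = F(IG) − F(CG). Net difference = forward-only difference − c × [b(IG) − b(CG)], where b is the proportion of contemplators moving back. Test: z = difference / √[2p(1 − p)/471], where p is the mean of the two proportions.

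- *(a) Offsetting effects.* IG forward 28%, with backward moves rising by the same 8 points of the arm. Here p = 0.24 and z = 0.08 / √(2 × 0.24 × 0.76 / 471) = 2.87, p-value 0.004. The forward-only outcome shows +8 points while the net difference is 0. This needs b(IG) = 0.10 + 0.08/c.
- *(b) Backward effect only.* Forward 20% in both arms; b rises from 10% to 25%. The forward-only difference is 0 (p-value 1.0). Net difference = −0.15c.
- *(c) Mixed.* IG forward 28%; b rises from 10% to 40%. The forward-only difference is +8 points (p-value 0.004). Net difference = 0.08 − 0.30c.

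| Contemplator share c | (a) b(IG) needed for net 0 | (b) net difference, points | (c) net difference, points |
|---|---|---|---|
| 20% | 50% | −3.0 | +2 |
| 30% | 37% | −4.5 | −1 |
| 50% | 26% | −7.5 | −7 |
| 70% | 21% | −10.5 | −13 |

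In (b), counting backward moves would reveal the effect. At c = 20% the backward proportions are 2% versus 5% of the arm (p-value 0.012); at c = 70% they are 7% versus 17.5% (p-value below 0.001).

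**Check on plausibility.** Suppose regression were confined to light smokers. The Background implies that 100 − 79 = 21% of male and 100 − 70 = 30% of female daily smokers smoke 10 or fewer cigarettes a day. If light smoking is independent of phase, light-smoking contemplators at c = 50% are 10.5% to 15% of the arm. An extra 8 points of backward moves then means 8/15 = 53% to 8/10.5 = 76% of them regressing beyond the control rate. At c = 30% it is 8/9 = 89% to 8/6.3 = 127%, the latter impossible. At c = 70% it is 8/21 = 38% to 8/14.7 = 54%. Full offsetting as in (a) would therefore need an extreme effect if only light smokers regressed.

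**The case against.** Forward progression is a legitimate responder endpoint when compared between randomised arms. Backward moves can be derived from data already planned. False reassurance could also show as fewer quitters or less reduction in cigarettes, both of which are compared between arms. A condensed article may leave the scoring of unlisted transitions to a fuller document.

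Much of this stands, and it limits the point. Four stronger readings are tempting, and the document does not support them:

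- *The protocol expects backward moves.* It does not say so. The oscillation in the Study population section describes ambivalence within contemplation. The Discussion names a limitation of studies of personal risk and does not mention phase regression.
- *Backward moves are scored as no change.* That is the natural reading of a list of qualifying moves, but no scoring rule is written.
- *Brief advice cannot protect against false reassurance because both arms receive it.* The Discussion claims only that advice given alongside the reading softens the effect of a normal one. Giving the same advice to controls does not contradict that.
- *The trial hides its one adverse effect and cannot answer its motivation objective.* This goes too far, since the data would exist and other outcomes could show harm.

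What the objection does not remove is the mismatch itself. The article fixes the definition of this outcome, and that definition cannot register regression. Data that could be re-analysed later do not replace a prespecified two-way outcome.

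**Conclusion.** The point holds as a mismatch between a direction-neutral objective and a forward-only secondary outcome. If CO feedback moved some intervention-group contemplators backward, the outcome could look neutral or favourable while net motivation was unchanged or worse.

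Its size is unknown. The illustrations rest on assumed transition rates and an assumed contemplator share. The effect is small when contemplators are few, and in scenario (c) at a 20% share the net change stays positive. The illustrations show what the definition would miss; they do not forecast what will happen. The primary outcome, the sample size and the conduct of the trial are unaffected. The change is worth making before analysis because it costs almost nothing and avoids a later, data-driven choice.

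**What to change.** Under Secondary outcome measures, define phase change from baseline at months 6 and 12 as forward, unchanged or backward. Count cessation as the most advanced phase, because a move to cessation is also absent from the list and quitters would otherwise have no place. Compare the arms on this ordered three-level outcome; the Statistical analysis section already allows non-parametric tests. Report the forward and backward proportions by arm, with the full baseline-by-follow-up phase table for each arm.

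Any breakdown by baseline ppm within the intervention group should be descriptive only. It is not a randomised comparison, CO level is tied to consumption, and the control group has no baseline reading to set beside it.

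The cost is the rewording of one secondary outcome and slightly more analysis. No new data are needed. Phase is recorded at baseline and the dependent measures are collected again at 6 and 12 months. The outcome as planned must already tell pre-contemplation from contemplation at follow-up, because a move between them is on its list.

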#### Independent measures

Type of intervention: brief advice or brief advice together with CO-oximetry. At baseline, the following information will be obtained: (a) socio-demographic variables: gender, age, social class measured by means of two indicators suggested by the Spanish Society of Epidemiology: educational level and occupation; (b) regarding the patient’s smoking behaviour: number of cigarettes/day and number of years the patient has been smoking (the number of packets/year will be calculated based on this information); concentration of nicotine and tar smoked currently (obtained from the type of tobacco consumed); number of times the patient has tried to quit smoking and reasons for relapse; maximum amount of time without smoking; tobacco consumption during work, with family and/or friends; physical dependency on nicotine using a simplified version of the Fagerström test; phase of the smoking cessation process: Prochaska and DiClemente phases (pre-contemplation, contemplation, preparation, cessation and relapse); any intervention to quit smoking during the past year; (c) other measures: consumption of other legal drugs (alcohol, psychopharmacological drugs); consumption of illegal drugs (cannabis, cocaine and others); basal disease associated with tobacco consumption (Chronic Obstructive Lung Disease, cancer, ischemic myocardiopathy, cerebrovascular disease); other cardiovascular risk factors (HTA, diabetes mellitus, dyslipidaemia, obesity); mental illness.

At months 6 and 12 the following data will be collected: Smoking behaviour/status (does the patient smoke or has he/she quit); date of smoking cessation, whether the patient has quit smoking; time interval without smoking between date of intervention till six month assessment; participation in a programme for smoking cessation since the beginning of the study.

### Study development

*a).* A pilot study will be carried out in two health centres to proceed with the creation of the final DCB based on comments and suggestions from the GP and nurse participants. *b).* Training will be given to the professional participants in the study regarding brief advice and how to carry out the CO-oximetries to ensure that data collection is as homogeneous as possible. The nursing staff contracted for the development of the evaluations will also receive this training. *c).* A total of 3 contacts with each subject will be carried out. The first contact: inclusion-intervention visit will be carried out by the health centre’s professional participants. Two assessment contacts: a 6 month phone assessment and a final assessment at 12 months in the health centre will be performed by the nursing staff contracted for the study who will not have any knowledge of the randomisation scheme. *d).* On the first visit, once the subject has signed the informed consent and been randomised, baseline information will be collected by means of the basal DCB (socio-demographic variables, smoking habits variables, and other variables related to the consumption of drugs, diseases and cardiovascular risk factors). Subsequently, the intervention will be carried out. *e).* Six months after inclusion, the independent and dependent measurements mentioned above will be collected by means of another DCB by phone. *f).* the final assessment will be carried out at 12 months. The DCB will contain the same questions as those administered at 6 months, the urine cotinine test will be used to confirm sustained smoking cessation in those claiming to have quit smoking, and a CO-oximetry will be performed on patients in both groups. g). If a subject requests help to quit smoking during the study, he/she will be aided and referred to his/her GP or nurse to proceed with the intervention. This information will also be recorded.

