### Recruitment of subjects

Every person consulting a general practitioner (GP) or a nurse will be asked about their smoking behaviour and their attitude toward quitting smoking. To establish the patient’s phase or period of change, he/she will be asked the following: “have you ever seriously thought that you should quit smoking within 1 month?”, following the model of question used in the ISTAPS project [24].

If the subject fulfils the inclusion criteria, information on the study will be released, the subject invited to participate and, upon acceptance, will provide signed informed consent. Subsequently, the participant will be randomised to either CG or IG.

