### Random allocation to study arms

The randomised scheme will be carried out in blocks of 20, using a computer program. The allocation of each patient will be determined using a table of randomised numbers, and this number will be indicated on a report placed in closed, opaque envelopes sequentially numbered. Each professional will have 20 envelopes, one for each subject. The professional will not know the randomisation scheme. The socio-demographic variables, together with those on the smoking habits of the participants that decline to participate in the study, will be collected in a separate report. The inclusion period for subjects will be 12 months.

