### Intervention

The intervention applied to the CG will be brief advice, which will be serious, firm, concise, personalised and appropriate for the phase of change. The brief advice attempts to encourage subjects in a clear, firm and personalised way to quit smoking, inform more than oblige, facilitate information on the negative effects of tobacco on health, highlight the main advantages of quitting smoking and ask them to identify and examine the main obstacles when quitting smoking. Once the brief advice to stop smoking has been carried out verbally, the patients will be given a written document with advice and several guidelines. The healthcare professionals will receive training on how to give the brief advice.

In the IG, apart from giving the brief advice in exactly the same way as for the CG, a CO-oximetry test will also be carried out on each subject. Before it is performed, the basics of the test and what it measures will be explained to patients. Once the subject has properly understood how the technique works and if he/she is at an optimum moment for it to be carried out (having not smoked one hour prior to the test/having not smoked for more than 10 hours), the levels of carbon monoxide in expired air will be measured in parts per million (ppm) and recorded in the data collection booklet (DCB) and in a personal report that will be given out to the subject, together with an explanation and definition of CO-oximetry and an interpretation of the possible results.

The two interventions will be carried out by the healthcare professional including the patient in the trial, irrespective of whether he/she is a GP or a nurse. It will only be performed once, during the first visit following the inclusion of the patient into the study. Each professional will conduct one intervention or the other, depending on what intervention is assigned to the subject during randomisation.

The evaluation at months 6 and 12 will be done by a nurse blinded to patient allocation. At 6 months there will be a telephone evaluation and at 12 months an evaluation in the primary health centre.

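### The baseline booklet is filled in after randomisation by the professional who delivers the assigned arm, so the reference values for two secondary outcomes can be recorded with the arm known

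*Protocol article*

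**What the plan says.** The order of the first visit is fixed in the protocol article under Study development, item d: "once the subject has signed the informed consent and been randomised, baseline information will be collected by means of the basal DCB". The next step is "Subsequently, the intervention will be carried out". Recruitment of subjects gives the same start: after consent, "Subsequently, the participant will be randomised to either CG or IG".

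The staffing is also fixed. Study development, item c, says that the "inclusion-intervention visit will be carried out by the health centre’s professional participants". The Intervention section says that "The two interventions will be carried out by the healthcare professional including the patient in the trial", and that "Each professional will conduct one intervention or the other, depending on what intervention is assigned to the subject during randomisation". Under Random allocation to study arms, each professional has a personal set of 20 sealed, numbered envelopes, and "The professional will not know the randomisation scheme".

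Blinding is described for follow-up only: "The evaluation at months 6 and 12 will be done by a nurse blinded to patient allocation".

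Independent measures lists daily cigarette consumption and the Prochaska and DiClemente phase among the baseline variables. Secondary outcome measures includes reduction in self-declared cigarettes among those who have not quit, and movement to a later phase, each at 6 and 12 months.

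**The concern.** Baseline values used to compute change should be recorded before anyone in the room can know the arm. Here they are recorded afterwards, by the person who is about to deliver that arm. Cigarettes per day is a self-report taken by that person, and phase is that person's classification of what the patient says, so both leave room for judgement. If they are recorded even slightly differently in the two arms, the difference enters the change outcomes and looks like a treatment effect. Masking the assessor at 6 and 12 months protects only the follow-up half of the comparison.

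Two results are at stake: the cigarette-reduction and phase-change outcomes, which the Background names as study aims, and the smoking-related rows of the baseline table, where a difference between arms could no longer be put down to chance alone.

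**Working it through.** **Can the recorder know the arm?** Reading the sections together:

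1. Order of steps: consent, randomisation, baseline booklet, intervention (Study development, item d).
2. The professional who includes the patient runs this visit and delivers whichever arm was assigned (Study development, item c; Intervention), so must learn the individual allocation.
3. The concealment wording covers the scheme, meaning assignments still to come. It does not hide the current patient's allocation once that patient is randomised.
4. No blinding is stated for the first visit.

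So the arm can be known when the booklet is completed. The text does not say at what moment the envelope is opened; that it is open before the booklet is the natural reading of a patient who has already been randomised.

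**Which outcomes use the exposed values?**

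| Outcome | Uses a baseline value? |
|---|---|
| Sustained cessation, cotinine-confirmed (primary) | No |
| Point cessation, cotinine-confirmed | No |
| Self-declared cessation | No |
| Reduction in cigarettes | Yes: cigarettes per day |
| Change of phase | Yes: phase |

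For phase, the route follows from the definition. A patient found in contemplation at follow-up counts as progress if the baseline entry was pre-contemplation, but not if it was contemplation. Choosing between those two entries at baseline therefore alters the chance of a success.

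**The plan's own figure.** With 5% against 10%, two-sided alpha 0.05 and power 0.80, the arcsine formula n = 2(1.96 + 0.842)² / h², where h = 2·asin(√0.10) − 2·asin(√0.05), gives 423.7 per group. Dividing by 0.90 gives 470.8, so the stated 471 is reproduced. The point does not depend on this figure; it only supplies the number followed up, 471 × 0.90 ≈ 424 per arm.

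**Illustration for cigarettes.** The documents give neither an SD of change nor a shift, so both are assumed. The calculation takes a raw change score compared between arms by a two-sided 5% test, with no true effect.

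- SE = SD × √(2/n) = 8 × √(2/424) = 0.549.
- False-positive rate = Φ(−1.96 + δ/SE) + Φ(−1.96 − δ/SE), where δ is the arm-dependent shift at baseline.
- δ = 0: 5%.
- δ = 0.5: δ/SE = 0.91, rate 14.9%.
- δ = 1: δ/SE = 1.82, rate 44.4%.

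Range over the assumed SD, at 424 per arm:

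| Shift (cigarettes/day) | SD 6 | SD 8 | SD 12 |
|---|---|---|---|
| 0.5 | 23% | 15% | 9% |
| 1.0 | 68% | 44% | 23% |

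The outcome applies to non-quitters only. Removing 5% of 424 leaves about 403 per arm; at SD 8 the rates become 14.4% and 42.6%, much the same.

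**The case against.** The case for a small point is good, and most of it stands.

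- **Phase is screened before randomisation.** Recruitment of subjects asks about smoking behaviour and attitude to quitting before consent, so exclusion of the preparation phase is settled before allocation. This stands. However, the quoted screening question has a one-month horizon and does not by itself separate pre-contemplation from contemplation, which the phase outcome needs. No pre-randomisation record of cigarettes per day is stated.
- **The CO result cannot contaminate baseline.** The booklet precedes the intervention, so this stands. A reader might infer that intervention-group patients answer while already expecting a CO test. The documents do not support that: the explanation of the test belongs to the intervention, which comes after the booklet, and nothing says that the patient learns the arm earlier. The supported route is recording by the professional.
- **Adjusted analyses.** A reader might infer that a baseline-adjusted model is compromised. Statistical analysis specifies none; it names t, chi-squared and non-parametric tests.
- **Withdrawals.** A reader might infer that randomised patients will lack baseline data. All the steps fall within one visit, so the window is short, and anyone lost counts as a smoker in the intention-to-treat analysis of cessation.
- **The whole baseline table.** Age, gender, education, occupation and recorded diagnoses are hardly open to arm-dependent recording. Only the smoking-related rows are exposed.
- **The magnitude is hypothetical.** This also stands. Nothing in the documents shows that the shift differs from zero or which arm it would favour. The reduction metric is not defined, and a non-parametric test may be used instead of a t test.

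**Conclusion.** The point holds as an avoidable sequencing weakness confined to two secondary outcomes and the smoking-related baseline rows. It rests on one inference, that the envelope has been opened when the booklet is filled in.

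A reader might go further and take the trial's main result to be at risk. It is not: cotinine-confirmed cessation needs no baseline value, and the sample size is unaffected. Nor should 15% or 44% be read as this trial's error rate. The arithmetic is right, but each figure comes entirely from an assumed SD and an assumed shift. What the figures show is that a small difference in recording, if it occurred, would matter for the cigarette outcome in a trial of this size. No comparable figure can be given for phase, because the documents give no phase proportions.

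**What to change.** Reorder item d of Study development to: consent, complete the baseline booklet, open the next envelope, deliver the intervention. Amend Recruitment of subjects to match, so that the booklet stands between consent and randomisation.

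The cost is a change of order within one visit. Staff, form, number of contacts and sample size stay the same. If the order is to be verifiable, the booklet's completion time and the envelope number could be noted.
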